The DPS technique, developed by [name], a senior physical therapist from Korea with over two decades of clinical experience, and [name], Director of the Rehabilitation Medicine Department at Qingdao University Affiliated Hospital, introduces a novel joint movement method known as “shear motion.” This approach has demonstrated promising therapeutic effects in pain relief and neurorehabilitation (11–13). DPS begins with a structured postural assessment performed in the patient’s neutral stance to identify primary contributors to joint misalignment. Its foundation lies in the 4R technique: Resetting Joint Malalignment (RJM) corrects abnormal joint alignment; Resetting Abnormal Muscle Function (RAM) restores muscle performance; Resetting Joint Stabilization (RJS) re-establishes joint stability; and Resetting Sensory-Motor Control (RSMC) targets improvements in sensory and motor regulation. These combined interventions offer a multi-faceted strategy for correcting joint dysfunction and reestablishing functional movement.

In our clinical experience, supported by patient feedback, the DPS method has shown a clear capacity to reduce post-stroke shoulder pain, improve shoulder range of motion, and promote functional recovery of the hemiplegic limb. Encouraged by these observations, we have initiated a large-scale trial to assess the comparative effectiveness of DPS in patients experiencing symptomatic post-stroke shoulder pain. We hypothesize that DPS will demonstrate greater efficacy than SCTT. The goal of this study is to evaluate DPS as a potentially more effective treatment that not only reduces pain but also improves shoulder mobility and minimizes functional impairments that affect the quality of life in millions of stroke survivors with hemiplegia.

This paper outlines the design and protocol of the first randomized controlled trial directly comparing DPS with SCTT for managing post-stroke shoulder pain. The study aims to fill an important evidence gap and offer practical guidance for clinical treatment of this complex condition. Results will be published in compliance with the Consolidated Standards of Reporting Trials (CONSORT) guidelines (14), ensuring transparency and methodological soundness.

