### Sample size calculation

This study draws on findings from a previously published clinical observational trial on the application of DPS for post-stroke shoulder pain (15). Sample size estimation was performed using G*Power 3.1 software. The significance level (*α*) was set at 0.05, *β* at 0.20, and statistical power (1−β) at 0.80. Based on the method for comparing two groups of equal size and using an effect size (Cohen’s d = 0.91) as reported in the referenced study, the minimum required number of participants was calculated to be 19 per group, totaling 38. To account for an expected dropout rate of 20%, the sample size was increased to 48 participants. This adjustment ensures sufficient statistical reliability and helps maintain the study’s validity despite potential participant attrition.

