### Data analysis

Statistical analyzes will be performed using SPSS version 27.0. All continuous variables will be tested for normality using the Shapiro–Wilk test. Normally distributed data will be expressed as mean ± standard deviation and analyzed using independent sample *t*-tests for between-group comparisons and repeated measures ANOVA for within-group comparisons across time points (baseline, week 2, week 4, and 1-month follow-up). Non-normally distributed data will be reported as medians with interquartile ranges and assessed using the Mann–Whitney U test and Friedman test, respectively. Categorical variables such as gender or stroke type will be analyzed using chi-square tests or Fisher’s exact tests when appropriate. A two-sided *p*-value < 0.05 will be considered statistically significant for all analyzes.

For musculoskeletal ultrasound outcomes, four key indicators will be analyzed: (1) distance from the acromion to the greater tuberosity of the humerus and (2) thickness of the subdeltoid bursa will be treated as continuous variables and analyzed using the same approach as other quantitative measures—independent *t*-tests or Mann–Whitney U tests for between-group comparisons, and repeated measures ANOVA or Friedman tests for within-group changes. (3) Calcifications in the supraspinatus tendon and (4) effusion around the long head of the biceps tendon sheath will be treated as binary variables (presence/absence) and compared between groups using chi-square tests. All ultrasound images will be independently reviewed by two experienced sonographers blinded to group allocation. Inter-rater reliability will be evaluated using Cohen’s kappa for categorical variables and intraclass correlation coefficients (ICC) for continuous variables. Any discrepancies will be resolved by consensus discussion.

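### Repeated-measures methods are used only within each arm, so no stated analysis compares the DPS and SCTT time courses or adjusts for baseline VAS

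*Protocol article*

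**What the plan says.** All of the following is in the protocol article.

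- **Aim.** The Introduction is comparative: "We hypothesize that DPS will demonstrate greater efficacy than SCTT".
- **Primary outcome.** The Primary outcome section defines it as VAS change from baseline at three later times, which Table 1 places at weeks 2, 4 and 8.
- **Between arms.** Under Data analysis, normally distributed variables are "analyzed using independent sample *t*-tests for between-group comparisons".
- **Within arms.** The same sentence assigns "repeated measures ANOVA for within-group comparisons across time points (baseline, week 2, week 4, and 1-month follow-up".
- **Non-normal data.** The same division is kept: these are "assessed using the Mann–Whitney U test and Friedman test, respectively".
- **Ultrasound.** The division is repeated for the continuous ultrasound measures: "repeated measures ANOVA or Friedman tests for within-group changes".
- **Significance.** "A two-sided *p*-value < 0.05 will be considered statistically significant for all analyzes".
- **Dropout.** "To account for an expected dropout rate of 20" per cent, the Sample size calculation section raises 38 to 48.

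The article names no arm-by-time term, no ANCOVA and no mixed model. The Study design overview lists covariates and the Randomization section stratifies on stroke type and time since stroke, but none of the named tests for continuous outcomes is described as using them.

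**The concern.** The only method that uses all visits together is run one arm at a time, so it gives no estimate or test of DPS against SCTT. VAS can be expected to fall in both arms whatever the manual therapy does. Entry requires a VAS of at least 4, which invites regression to the mean. Recruitment partly draws on patients transferred about 10 days after the acute phase. Routine rehabilitation continues in everyone. A within-arm p-value mixes all of this with the treatment effect.

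The 0.05 threshold applies to every analysis, so the results will contain within-arm p-values for each arm next to the between-arm ones. A finding of significance in one arm and not the other is easily taken as evidence of superiority, which it is not. The Discussion also expects the benefit of DPS to last longer than that of tuina. That is a between-arm statement about time course, and no planned analysis addresses it as a whole.

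The between-arm tests that are planned take no covariates. They leave unused the precision that baseline VAS would give in a trial of 48.

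**Working it through.** **1. The plan's own figures.** Inputs from the Sample size calculation section: d = 0.91, α = 0.05, power 0.80; two-sided testing from Data analysis. With the normal formula, n per arm = 2 × ((1.960 + 0.842) / 0.91)² = 18.96, so 19 per arm and 38 in total. Dropout: 38 / (1 − 0.20) = 47.5, so 48. Both figures reproduce. Power at 19 per arm is 0.80 (normal) or 0.78 (exact t); at 24 per arm it is 0.87 (exact t). The sizing is for a two-group comparison at one time, not for a group-by-time test.

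**2. What within-arm tests show when the arms do not differ.** If each arm's test is significant with probability π and the arms are identical and independent, exactly one is significant with probability 2π(1 − π). This is 2 × 0.05 × 0.95 = 9.5% when nothing changes, peaks at 50% when π = 0.5, and returns to 0 as π nears 1.

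The simulation used 4,000 trials per row, 19 completers per arm and four visits, with equal correlation ρ between visits. Common mean change was 0, −0.5, −1 and −1 times the stated fall. The SD, correlation and fall are assumptions; the article gives none of them.

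| ρ | Common fall (SD) | Exactly one arm significant | Both significant | Group-by-time test rejects |
|---|---|---|---|---|
| 0.5 | 0 | 10.2% | 0.3% | 4.9% |
| 0.5 | 0.3 | 31.4% | 4.3% | 5.2% |
| 0.5 | 0.5 | 50.2% | 27.8% | 5.3% |
| 0.5 | 0.8 | 13.7% | 86.0% | 5.3% |
| 0.5 | 1.0 | 1.8% | 98.2% | 5.4% |
| 0.7 | 0 | 9.6% | 0.2% | 4.6% |
| 0.7 | 0.3 | 43.2% | 10.9% | 4.6% |
| 0.7 | 0.5 | 35.6% | 59.3% | 5.2% |
| 0.7 | 0.8 | 1.1% | 98.9% | 4.8% |
| 0.7 | 1.0 | 0.0% | 100% | 5.1% |

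Moderate common falls often give discordant arms; large ones make both arms significant, which is equally uninformative about the difference. The group-by-time test stays near 5% throughout.

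**3. Baseline adjustment.** Assume equal SD σ at each visit and the same ρ. The outcome variance entering the arm contrast at one visit is then:

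- raw score: σ²;
- change score: 2(1 − ρ)σ², which is 1.00σ² at ρ = 0.5 and 0.60σ² at ρ = 0.7;
- baseline-adjusted: (1 − ρ²)σ², which is 0.75σ² and 0.51σ².

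Against a t-test on change, adjustment cuts the variance by 25% at ρ = 0.5 and by 15% at ρ = 0.7 (0.51 / 0.60 = 0.85).

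**4. Missed visits.** On unimputed data, classical repeated-measures ANOVA and Friedman need a value at every visit. If each of the three post-baseline visits is missed independently with probability q (assumed), the complete patients number 48(1 − q)³:

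- q = 5%: 48 × 0.857 = 41.2;
- q = 10%: 48 × 0.729 = 35.0;
- q = 20%: 48 × 0.512 = 24.6.

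A t-test at a given visit still uses everyone seen at that visit.

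**The case against.** The strongest reply is that the arms are compared. The sentence that confines ANOVA to within-arm change also assigns t-tests, or Mann–Whitney U, to the between-arm comparison, and the trial is sized for a two-group comparison. Randomisation makes regression to the mean and natural recovery act on both arms alike, so those tests are valid. On this view the within-arm ANOVA is only a supplement. This stands, and it limits the point to a missing longitudinal, baseline-adjusted comparison.

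Four stronger readings are tempting, and the article supports none of them:

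- *Superiority will be judged by setting one arm's p-value against the other's.* Nothing says so. The risk is one of interpretation.
- *Patients with one missed visit will be dropped.* No missing-data rule for VAS is written. Listwise loss is the default behaviour of the named methods on unimputed data, and an analysis plan that is not shown may deal with it. It would affect the within-arm analysis only.
- *The 20% dropout erodes the planned power.* It is already in the 48: 48 × 0.8 = 38.4, against the 38 required.
- *Half of null trials would mislead.* About 50% is the peak of the range. Larger common falls take the figure to nearly zero.

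It can also be said that a t-test on change from baseline already uses baseline. It subtracts baseline but does not adjust for it, and it treats each visit separately.

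**Conclusion.** The point holds in a limited form. The plan has a valid between-arm test, but it is unadjusted and takes no account of the repeated measurements. The method that does use them answers no comparative question. This is a choice the article states, not a detail left to a further document.

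Within-arm p-values cannot support superiority. With identical arms, exactly one is significant in 0% to about 50% of trials, depending on the assumed common fall (0 to 1 SD) and correlation (0.5 or 0.7), against about 5% for a group-by-time test. The precision given up by not adjusting for baseline is a variance reduction of 15% to 25% relative to a change-score t-test, under the same correlations and equal SDs. The loss from missed visits is conditional on unimputed data and does not affect the planned between-arm power. The change should be made before analysis, but the trial is not invalid without it.

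**What to change.** Make the between-arm analysis of VAS one linear mixed model for repeated measures on all randomised patients:

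- outcome: VAS at weeks 2, 4 and 8;
- fixed effects: arm, visit, arm-by-visit, baseline VAS, and the stratification factors (stroke type and time since stroke);
- covariance: unstructured, which has six parameters for three visits.

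Report the DPS minus SCTT contrast with a 95% CI at each visit. The sponsor should name one visit in advance as primary. Week 4, the end of treatment, is one candidate, but the article lists three times and the choice is the sponsor's. Use the same model for the continuous secondary outcomes at weeks 2 and 4, and label within-arm changes as descriptive only.

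The cost is protocol or analysis-plan wording and slightly more analysis work. No new data are needed, and the stated software is adequate ("Statistical analyzes will be performed using SPSS version 27.0"; its MIXED procedure fits this model). The model keeps patients with partial follow-up but relies on a missing-at-random assumption. A patient with no post-baseline VAS still contributes no outcome information.

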**Figure 1 fig1:**
[figure not shown]
Study design flowchart: a detailed depiction of participant progression through each stage of the study.

The primary outcome is pain intensity, assessed using the VAS, a widely recognized and validated tool. VAS scores will be recorded at baseline, at 2 and 4 weeks during treatment, and again at a 1-month follow-up after completion of the intervention. Secondary outcomes assess shoulder joint function across four domains. First, ROM will be measured to evaluate mobility of the affected shoulder. Second, the absolute vertical distance difference between the medial superior angle of the scapula on the affected side and the second thoracic spinous process will be recorded. Third, musculoskeletal ultrasound will be used to assess five key indicators: presence of effusion around the long head of the biceps tendon sheath, calcification in the supraspinatus muscle, calcification at the insertion of the subscapularis tendon, subdeltoid bursa thickness (in millimeters), and the distance from the acromion to the greater tuberosity of the humerus. Lastly, the MBI will be used to evaluate overall independence in daily living activities. Covariates include age, sex, body mass index (BMI), stroke type (hemorrhagic or ischemic), and time since stroke onset. All outcome measures will be collected at baseline, 2 weeks, and 4 weeks after treatment begins. A follow-up VAS will be conducted 1 month post-intervention to assess the sustained effects of DPS in relieving post-stroke shoulder pain. The physical function assessments will be performed by trained evaluators blinded to treatment allocation, and data analysis will be conducted by statisticians also blinded to group assignments.

Detailed outcome variables and their classification as endpoints or intermediate measures are summarized in Table 1.

**Table 1 tab1:** Baseline assessment and sequence of trial measurements for primary and secondary outcomes.

	Before-intervention	Mid-intervention	Post-intervention	1-month follow-up
Time (weeks)	**0**	**2**	**4**	**8**
Baseline				
Sex (male/female)	**√**			
Type of stroke (ischemia/hemorrhage)	**√**			
Age, y	**√**			
BMI	**√**			
Time since stroke, y	**√**			
Primary outcome variable				
VAS	**√**	**√**	**√**	**√**
Secondary outcome variables				
Shoulder ROM				
Flexion (0–180°)	**√**	**√**	**√**	
Extension (0–50°)	**√**	**√**	**√**	
Abduction (0–180°)	**√**	**√**	**√**	
Adduction (0–40°)	**√**	**√**	**√**	

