## Discussion

This study presents a rigorously designed randomized controlled trial protocol comparing the efficacy of Discovery of Posture Secret manual therapy with Standardized Chinese Tuina Therapy in patients with PSSP. As a common and functionally disabling complication in stroke survivors, PSSP remains a challenge to effective rehabilitation. The trial’s design integrates both subjective and objective outcome assessments, with a particular emphasis on incorporating musculoskeletal ultrasound to enhance the objectivity and clinical relevance of the evaluation process. The combination of a novel intervention approach and a multimodal outcome framework represents a comprehensive strategy to address this complex condition.

While SCTT remains a widely practiced and guideline-supported therapy for shoulder pain in China, it is primarily focused on local muscle relaxation and relies heavily on therapist experience. In contrast, DPS introduces a structured, biomechanically informed manual therapy model aimed at restoring joint alignment, reactivating neuromuscular control, and enhancing postural stability. By systematically addressing joint malalignment, abnormal muscle recruitment, and proprioceptive deficits, DPS is expected to offer broader and more sustained functional benefits compared to conventional tuina. The structured nature of DPS may also contribute to improved reproducibility and standardization in clinical practice, a longstanding challenge in traditional manual therapy.

The outcome framework of this trial includes one primary and several secondary measures, designed to reflect both patient-reported symptoms and functional recovery. Pain intensity, measured by the VAS, serves as the primary outcome due to its direct relevance to patient experience and its sensitivity to change. Secondary outcomes such as shoulder joint ROM, scapular alignment (quantified by the vertical distance to the T2 spinous process), musculoskeletal ultrasound, and the MBI are essential for capturing improvements in joint function and daily living capacity. Together, these indicators provide a multifaceted understanding of how different therapeutic strategies impact recovery.

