A notable innovation in this study is the use of musculoskeletal ultrasound as an objective and structural assessment tool. Traditional evaluations of PSSP have largely relied on subjective scales or clinical observation, often lacking precise anatomical insight. In contrast, musculoskeletal ultrasound enables visualization and quantification of structural abnormalities such as subdeltoid bursa thickening, calcifications in the rotator cuff tendons, effusion around the long head of the biceps tendon, and reduced acromion-to-greater tuberosity distance. These structural changes are closely linked to pain and dysfunction in PSSP, and their inclusion in the outcome set allows for a more granular evaluation of treatment effects. Moreover, blinded dual-sonographer image assessment and the use of inter-rater reliability analysis contribute to the scientific rigor and reliability of these imaging outcomes.

Beyond its role as a diagnostic and monitoring tool, musculoskeletal ultrasound may also provide insight into the underlying mechanisms through which manual therapies exert their effects. For instance, a reduction in bursal thickness or tendon effusion following DPS intervention may suggest not only symptom relief but also a genuine reversal of soft tissue inflammation or mechanical impingement (24). In this way, ultrasound imaging serves not only as a clinical endpoint but also as a potential biomarker of therapeutic response, paving the way for mechanism-based rehabilitation research.

From a biomechanical perspective, DPS offers a compelling theoretical framework for addressing the pathophysiology of PSSP. Abnormal postural patterns and joint malalignment—such as thoracic rotation, scapular depression, or glenohumeral instability—are common in stroke survivors due to neuromuscular imbalance and compensatory movement (19). The four core components of DPS—Resetting Joint Malalignment, Resetting Abnormal Muscle Function, Resetting Joint Stabilization, and Resetting Sensory-Motor Control—are designed to systematically correct these dysfunctions. By restoring normal scapulothoracic and glenohumeral relationships, DPS may reduce secondary impingement, redistribute mechanical loads, and re-establish efficient motor patterns. The integration of biomechanical correction with sensorimotor retraining is particularly relevant in stroke rehabilitation, where central and peripheral impairments often coexist.

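### One p < 0.05 rule for every analysis covers 14 unranked secondary measures, so the risk of a false functional or structural claim is materially inflated

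*Protocol article*

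**What the plan says.** Pain on the VAS is the only primary outcome. For the rest, the Study design overview says: "Secondary outcomes assess shoulder joint function across four domains". The domains are ROM, scapula–T2 distance, musculoskeletal ultrasound and MBI. Table 1 gives each of the eight ROM directions its own row. Tables 1 and 2 schedule all secondary outcomes at baseline, week 2 and week 4, while the Abstract places them at 4 weeks.

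The Data analysis section compares the arms by t-test or Mann–Whitney test on continuous variables and by chi-square test on binary ultrasound findings. It closes its general paragraph with one threshold: a two-sided p-value "< 0.05 will be considered statistically significant for all analyzes". No lead ROM direction, key secondary outcome, testing order, division of alpha or exploratory label appears. The word *key* is attached to the ultrasound indicators as a set and ranks none of them.

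The article also looks to these outcomes for comparative benefit. The Introduction sets the goal of evaluating DPS as a potentially more effective treatment that "not only reduces pain but also improves shoulder mobility and minimizes functional impairments". The Discussion says that "DPS is expected to offer broader and more sustained functional benefits compared to conventional tuina" and that "ultrasound imaging serves not only as a clinical endpoint but also as a potential biomarker of therapeutic response".

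**The concern.** A 5% error rate belongs to one test. When many secondary comparisons each carry the same threshold, and nothing says which of them counts, the chance that at least one crosses it by luck is well above 5%. With eight ROM directions and no lead, a single direction could be reported as better mobility under DPS. A single ultrasound indicator could likewise be reported as a structural benefit.

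At stake is what the trial may conclude about function and structure. The primary VAS analysis and the sample size are not affected.

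**Working it through.** **The plan's own figure.** The Sample size calculation section gives alpha 0.05, "and statistical power (1−β) at 0.80" and an "effect size (Cohen’s d = 0.91) as reported in the referenced study"; it reports that "the minimum required number of participants was calculated to be 19 per group, totaling 38". The normal-approximation formula reproduces this: n = 2 × (1.960 + 0.842)² / 0.91² = 18.96, so 19 per group. Allowing for 20% dropout, 38 / 0.80 = 47.5, so 48. This is one comparison at 0.05. No effect size or alpha is set aside for any secondary outcome.

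**Counting the family.** Measures with a stated analysis:

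| Domain | Measures |
|---|---|
| ROM directions | 8 |
| Scapula–T2 distance | 1 |
| Ultrasound indicators in Data analysis | 4 |
| MBI | 1 |
| Total | 14 |

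The Study design overview and Table 1 list a fifth ultrasound indicator, subscapularis calcification. The Data analysis section names four and omits it, so it is not counted. Week 4 alone gives 14 between-arm tests. Weeks 2 and 4 together would give 14 × 2 = 28.

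**Independent tests, no true difference.**
- Any false significance: 1 − 0.95^14 = 51%; 1 − 0.95^28 = 76%.
- At least one falsely favouring DPS (2.5% per test): 1 − 0.975^14 = 30%; 1 − 0.975^28 = 51%.
- Expected false positives in either direction: 14 × 0.05 = 0.7; 28 × 0.05 = 1.4.

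**Correlated tests.** The outcomes are surely correlated, but the article gives no correlations, so a range is assumed. Let each test statistic be √ρ·Z + √(1−ρ)·e_j, with Z shared by all tests and e_j specific to one, all standard normal and scored so that a positive value favours DPS. With c = 1.96:

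- any false significance = 1 − E_Z{[Φ((c − √ρZ)/√(1−ρ)) − Φ((−c − √ρZ)/√(1−ρ))]^k}
- any falsely favouring DPS = 1 − E_Z{[Φ((c − √ρZ)/√(1−ρ))]^k}

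| Family | Error | ρ = 0.3 | ρ = 0.5 | ρ = 0.7 |
|---|---|---|---|---|
| Week 4, k = 14 | either direction | 44% | 35% | 25% |
| Week 4, k = 14 | favouring DPS | 22% | 17% | 12% |
| Both visits, k = 28 | either direction | 64% | 49% | 33% |
| Both visits, k = 28 | favouring DPS | 34% | 25% | 17% |
| Eight ROM directions, one visit | either direction | 30% | 25% | 19% |

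**Cross-check.** A simulation of 20,000 trials per setting used 24 per arm, t-tests, and all outcomes treated as continuous. For 14 measures at week 4 it gave 44%, 35% and 25% in either direction, and 23%, 18% and 13% favouring DPS. Over two visits, with correlation 0.5 to 0.7 between visits, it gave 67% down to 39% in either direction and 37% down to 19% favouring DPS.

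**Relative to nominal.** At week 4 the DPS-favouring error is 12.4 / 2.5 = 5 times to 22.4 / 2.5 = 9 times the rate of a single test.

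**The case against.** The strongest reply is that VAS is the sole primary outcome, so the word secondary already ranks the rest below it. Unadjusted secondary outcomes are common and acceptable when read as supportive. A condensed article may leave multiplicity to an analysis plan not shown, and the threshold can be taken as the usual nominal one. The Introduction and Discussion statements are aims and expectations, not rules for making claims.

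Part of this stands. Leaving out a multiplicity scheme would not by itself be a finding. But the article does more than leave it out: it declares the same significance rule for every analysis, and nowhere says that secondary results are only supportive. A later plan that ranked or downgraded them would have to depart from that sentence.

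Several stronger readings are tempting and are not supported:

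- **A false claim is likely.** The relevant harm is a false result in favour of DPS. At week 4 that is 12% to 22% with correlated outcomes and 30% if independent, which is inflated but not likely.
- **Error is about ten times nominal.** That comes from 28 tests, both directions and correlation 0.5 (49% against 5%). It is not the risk of a false superiority claim for DPS.
- **28 between-arm tests are fixed.** The visits in the Data analysis section are attached to the within-group repeated-measures analysis, and the Abstract names 4 weeks. A between-arm test at week 2 is an inference.
- **Every secondary outcome is tested.** Subscapularis calcification has no stated analysis.
- **A secondary result may replace a failed VAS.** Nothing says so, although nothing rules it out.
- **Ultrasound will demonstrate reversed inflammation.** The Discussion says only that a reduction may suggest it.

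**Conclusion.** The point holds as a defect in a stated rule. The consequence is a material inflation of the risk of a false functional or structural claim: at week 4, about five to nine times the single-test rate over the assumed correlations, and more if week 2 is also compared between arms.

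These sizes assume no true difference on any secondary measure, a common correlation of 0.3 to 0.7, and tests that reject at exactly their nominal level. The two binary ultrasound items would contribute somewhat less if exact tests were used at 19 to 24 per arm. A true effect on some measures would leave fewer on which a false positive is possible. Neither changes the conclusion. It should be corrected, but it does not threaten the primary result.

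**What to change.** In the Data analysis section, replace the threshold for all analyses with wording to this effect:

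- Two-sided p < 0.05 is the confirmatory criterion for the primary VAS analysis only.
- All secondary outcomes (ROM, scapula–T2 distance, ultrasound, MBI) are supportive or exploratory. They are reported as between-arm differences with 95% confidence intervals and nominal p-values, and cannot alone support a claim that DPS is superior to SCTT.

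If the sponsor wants a confirmatory functional claim, it may optionally name one key secondary measure at week 4 in advance, tested only if the VAS analysis succeeds. That keeps its false-positive chance at no more than 5% two-sided, or 2.5% in favour of DPS. A longer testing sequence is a design choice that this point does not require. A Bonferroni correction over 14 measures would be costly: with 24 per arm, and if d = 0.91 applied to a secondary outcome (an assumption), t-test power would fall from 87% at 0.05 to 54% at 0.05 / 14 = 0.0036.

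The change needs no new data or patients and leaves the sample size as it is. The Discussion need not be rewritten. The one downside is that an isolated secondary p < 0.05 can no longer be presented as a demonstrated benefit.
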